## Abstract

**Background:**

Breast cancer is the most common type of cancer in women worldwide, and its incidence is increasing. Although breast cancer survival is slowly increasing, related sequelae can persist after the disease has been treated. The main physical symptoms associated with breast cancer survival include pain, lymphedema, and associated functional limitations. Although multiple treatments are available for alleviating symptoms in breast cancer survivors, their effectiveness remains limited. Motor imagery (MI) and action observation (AO) therapies, which are based on the theory of motor simulation and are used in multiple fields with satisfactory results, have been proposed as alternatives for treating pain and improving mobility and strength.

**Objective:**

This study aims to design, implement, and evaluate the effectiveness of a program combining MI and AO therapies to improve functionality and mobility and alleviate pain and lymphedema of the affected upper limb in women who have survived breast cancer.

**Methods:**

A randomized controlled clinical study will be conducted in a sample of 108 participants who have experienced breast cancer and, as a result, have pain in the affected extremity, lymphedema, or loss of strength and/or mobility. The intervention group will include 54 participants managed with the MI and AO program (a combination of MI, AO, and mobility exercises), while the control group will consist of 54 women performing mobility exercises alone. Pain intensity, muscle strength, joint range, limb diameter, fear of movement, and imagery capability will be evaluated.

**Results:**

The intervention is expected to yield improvements in pain intensity, joint range, muscle strength, and symptoms associated with lymphedema, among other outcomes. The study was funded in December 2023. The number of participants recruited as of manuscript submission is approximately 80, and data analysis has not yet started. These results will be published in 2026.

**Conclusions:**

The implementation of an intervention based on MI and AO has the potential to positively impact female breast cancer survivors who face physical and psychological sequelae that interfere with their daily lives.

## Introduction

Worldwide, breast cancer accounts for approximately 23.8% of all malignant tumors in women, which establishes it as the most prevalent cancer in this population, with incidence rates continuing to rise [1]. Data from the International Agency for Research on Cancer of the World Health Organization indicate that, in 2022, a total of 2,296,840 new cases of breast cancer were diagnosed among women worldwide [1], with the 5-year global prevalence projected to rise to 8,178,393 cases [1].

The incidence of breast cancer continues to increase, and as mortality decreases, more patients live with the disease for longer, causing the prevalence to also increase [1,2]. According to the GLOBOCAN database, in 2020, the number of deaths worldwide among women with breast cancer was 684,996, representing 15.5% of all deaths from cancer. Improvements in treatments and prevention strategies have allowed for a reduction in mortality, mainly in African countries, but global lifestyle changes have driven an increase in disease prevalence [3]. As a result, the number of breast cancer survivors worldwide is increasing [2], creating significant challenges for long-term follow-up and the management of persistent symptoms [4].

Many breast cancer survivors continue to live with physical and emotional sequelae as a result of the treatments received and the oncological process itself. These late and persistent side effects not only compromise quality of life and functionality but may also prevent survivors from integrating the cancer experience into their daily lives [5]. Among the most common physical sequelae are pain, lymphedema, and postmastectomy syndrome. The latter is characterized by a burning sensation, tightness, stabbing, and pain in the chest, armpit, upper medial part of the arm, and surgical scar, characteristics similar to those of phantom limb syndrome. The likelihood of developing lymphedema is greater in women undergoing axillary lymphadenectomy, sentinel node biopsy, or mastectomy [6]. Lymphedema causes a decrease in the functionality of the affected arm, negatively impacting quality of life. This condition is estimated to affect 35% of patients and is associated with pain and functional limitations in activities of daily living (ADLs) [7].

Although it is one of the most frequent symptoms, pain secondary to breast cancer has not been sufficiently investigated [8]. It has been ascribed to a number of etiologies, such as cervical radiculopathy, rotator cuff tendinopathy, postmastectomy syndromes, or neuropathies, as well as preexisting comorbidities (back pain, arthritis, osteoarthritis, and axillary lymphadenectomy accompanied by chemotherapy and/or radiotherapy), young age (18-39 years), fibromyalgia, and depression or anxiety about the possibility of experiencing chronic pain [9]. There is existing evidence suggesting that breast cancer is associated with pain that can become chronic, affecting both patients and survivors.

Various interventions have been developed in an attempt to improve functionality and indirectly reduce pain [10]. Nonpharmacological strategies used in physiotherapy include multicomponent training (aerobic exercise, flexibility, and strength), neuromuscular bandaging, manual lymphatic drainage, and multimodal therapy. However, in many cases, the pain persists after the therapies have been completed [11].

In light of this situation, it is necessary to assess the effectiveness of emerging therapies, such as motor imagery (MI) and action observation (AO). Both interventions are based on simulation theory, which suggests that imagined or observed actions activate brain regions similar to those involved in the actual execution of the movement [12]. Specifically, MI is based on the fact that imagining the performance of an action stimulates the same parts of the brain map involved in performing the action itself [12]. This therapy has proven useful in various fields, such as sports, psychology, rehabilitation, medicine, and education [13]. Studies have reported beneficial effects of MI on the range of motion, strength, pain, and functionality of the affected limb [14-20]. For example, in the case of phantom limb syndrome, patients have reported a significant reduction in pain, which even disappeared in some cases [15]. There is recent randomized controlled trial evidence suggesting that MI-based interventions can increase physical activity levels and self-efficacy in women with breast cancer, supporting the potential of MI as a behavioral and rehabilitation strategy [21].

AO, meanwhile, is based on the hypothesis that, when observing the performance of an action or movement in the first or third person, the neural circuits involved in the execution of the action are activated [12]. This mechanism has been closely linked to the mirror neuron system, which responds during both execution and AO, providing a neurophysiological substrate for observational learning [22,23]. In other words, observing an action engages brain processes similar to those used when performing the action itself [12]. Similar to MI, AO has been applied in different disciplines and has shown positive results in the reorganization of action, motor control, and functional rehabilitation [24].

Individually, both MI and AO have demonstrated effectiveness in improving muscle strength, joint range, pain intensity, and functionality [15,19,24]. However, there is current evidence suggesting that their combined use produces greater activation of motor brain regions than when applied individually [25], although studies assessing the effectiveness of this combined therapy remain scarce [26]. A systematic review and meta-analysis published in 2025 has reported that combining both therapies effectively improves motor functionality, gait speed, upper-extremity functionality, pain intensity, and fear of movement, especially in the upper extremities [27]. Despite their promising potential, the application of these techniques within oncology—and especially among breast cancer survivors—has been insufficiently investigated, leaving a significant gap in the evidence base.

Therefore, the aim of this project is to design, implement, and evaluate the effectiveness of a program combining MI and AO therapies to improve functionality and mobility and alleviate pain and lymphedema of the affected upper limb in women who have survived breast cancer.

## Methods

### Design

A randomized controlled trial will be conducted to test the following hypothesis: a combination of MI and AO therapies is effective for improving mobility and alleviating pain and lymphedema of the upper limb in breast cancer survivors.

The protocol follows the SPIRIT (Standard Protocol Items: Recommendations for Interventional Trials) guidelines [28] and has been registered on ClinicalTrials.gov (NCT07067710). Future publications of the study results will be reported in accordance with the CONSORT (Consolidated Standards of Reporting Trials) guidelines [29].

### Setting

The study will be carried out in Navarra, an autonomous community and province in northern Spain. Information about the study will be disseminated through social networks and newspapers, and collaboration will be requested from SARAY, the Navarra Breast Cancer Association, a nonprofit regional association that promotes comprehensive care for women who have experienced breast cancer and provides biopsychosocial support through different services (eg, psychology, physiotherapy, and accompaniment).

### Study Participants and Eligibility Criteria

Female survivors of breast cancer who reside in Navarra will be invited to participate in the study. The inclusion criteria for participants in the study will be being female, being aged over 18 years, having a diagnosis of breast cancer, having completed any active cancer treatments (chemotherapy, radiotherapy, and/or immunotherapy), and being disease free at the time of data collection. Women undergoing hormonal therapy after treatment completion will also be included as hormonal treatment is not considered an active cancer therapy and is commonly prescribed among breast cancer survivors. Conversely, participants will be excluded if they have a diagnosis of cancer other than breast cancer or evidence of recurrence or metastasis requiring new treatment or are undergoing active cancer therapy (for recurrent or newly diagnosed disease).

### Sample Size

To determine the sample size, we assumed a type I error of 0.05 and a type II error of 0.20 (80% power). The calculation was based on a minimum detectable difference of 1.5 points in pain intensity measured using the numerical rating scale (NRS). This minimum difference aligns with established minimal clinically important difference values for the NRS in breast cancer–related pain contexts, which range from 1.39 to 2.0 points [30-33].

An estimated SD of 2.61 was selected based on a conservative approach considering the variability reported in breast cancer populations using the NRS, where SDs range from 1.4 to 2.8 [34-37]. This conservative estimate ensures adequate statistical power even if data dispersion is greater than anticipated. Considering an estimated 10% dropout, the required sample size was 108 women, with 54 allocated to the control group (CG) and 54 allocated to the intervention group (IG). The power calculations were performed using the GRANMO online program (version 7.12; Programa de Registre Gironí del Cor).

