### Randomization, Allocation, and Blinding

The participants in the study will be randomly assigned to 1 of 2 groups: the IG (MI+AO+mobility exercises) or the CG (mobility exercises alone). All the participants will perform mobility exercises of the upper limb involving flexion, extension, abduction, adduction, internal rotation, and external rotation for approximately 20 minutes between 1 and 3 times a day 3 times a week for the duration of the intervention (6 weeks).

The randomization process will be carried out using the Research Randomizer tool and an allocation ratio of 1:1 with the aim of guaranteeing impartiality and validity in the study and ensuring a balanced distribution, simple randomization, and a reduction in biases while preserving the integrity and reliability of the results. The randomization list will be created by a member of the research team without contact with participants or access to personal or clinical information.

This is a single-blind study, as neither participants nor the researchers delivering the intervention can be blinded. Blinding will be maintained for the researchers responsible for collecting outcome data, administering evaluation instruments, and performing the statistical analyses.

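### The sample size text guarantees adequate power under greater dispersion, but 108 women give 80% power after dropout only up to an SD of about 2.61, below the 2.8 at the top of the cited range

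*Protocol article*

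**What the plan says.** The Sample Size section of the protocol article takes a type I error of 0.05, 80% power and a minimum detectable difference of 1.5 points on the NRS. On variability it says: "An estimated SD of 2.61 was selected based on a conservative approach", with reference to breast cancer populations "where SDs range from 1.4 to 2.8". It then draws the conclusion at issue: "This conservative estimate ensures adequate statistical power even if data dispersion is greater than anticipated". The result is given as follows: "Considering an estimated 10% dropout, the required sample size was 108 women", that is, 54 per arm. The section on randomization confirms "an allocation ratio of 1:1". The Sample Size section reports no power at any SD other than 2.61.

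**The concern.** A sample size that just reaches 80% power at one SD has less than 80% at any larger SD. If 2.61 is the value at which 108 women reach 80%, the sentence promises a reserve that the number does not contain. The larger SD is not remote, because the protocol's own cited range runs to 2.8.

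What is at stake is how the result is read. Pain is the primary outcome and T1 the primary time point. If the observed SD comes out near the top of the cited range and the comparison is not significant, readers would set that result against a published assurance of power that the figures beside it do not support.

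**Working it through.** **Inputs**, all from the Sample Size section except the allocation ratio (randomization section): difference 1.5; SD 2.61; cited SD range 1.4 to 2.8; alpha 0.05; power 80%; dropout 10%; 54 per arm; 1:1. The calculation does not say whether alpha is two-sided. A two-sided test reproduces the stated number. A one-sided test does not (38 per arm, 43 after dropout, 86 in total).

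**Step 1: reproduce the stated size.**

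n per arm = 2 × (1.96 + 0.8416)² × 2.61² / 1.5² = 47.5, rounded up to 48.

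48 / 0.9 = 53.3, rounded up to 54 per arm, 108 in total. This is an exact match. (The noncentral t gives 49 per arm, 55 after dropout, 110 in total.)

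**Step 2: look for a reserve.** With 48 per arm, the largest SD that keeps 80% power is

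1.5 / (2.8016 × √(2/48)) = 2.62.

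The margin over 2.61 is about 0.01. With all 54 per arm analysed the limit is 1.5 / (2.8016 × √(2/54)) = 2.78, which is still below 2.8.

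**Step 3: power across the cited range.** Normal approximation: power = Φ(1.5 / (SD × √(2/n)) − 1.96). Noncentral t values are in brackets where computed.

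| SD | 48 per arm (after 10% dropout) | 54 per arm (no dropout) |
|---|---|---|
| 2.1 (midpoint of range) | 93.8% | 96.0% |
| 2.61 (used) | 80.4% (79.6%) | 84.8% (84.1%) |
| 2.7 | 77.7% (76.8%) | 82.3% |
| 2.8 (top of range) | 74.7% (73.8%) | 79.5% (78.8%) |

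For example, at SD 2.8 and n = 48: 1.5 / (2.8 × 0.2041) = 2.624; 2.624 − 1.96 = 0.664; Φ(0.664) = 0.747.

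**Step 4: detectable difference at SD 2.8 with 48 per arm.** 2.8016 × 2.8 × √(2/48) = 1.60 points.

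**Step 5: for scale only.** Keeping 80% power at SD 2.8 would take 2 × 2.8016² × 2.8² / 1.5² = 54.7, so 55 evaluable per arm; 55 / 0.9 = 61.1, so 62 randomised per arm and 124 in total (56, 63 and 126 by the noncentral t).

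**The case against.** The best defence is that the sentence can be read kindly. The SD of 2.61 sits (2.61 − 1.4) / (2.8 − 1.4) = 86% of the way up the cited range. If the anticipated dispersion means a typical cited value, the choice does protect: at the midpoint of 2.1, power is about 93–94%. This stands as far as it goes. Calling 2.61 a conservative choice is defensible, and a cautious value need not be the maximum. But the section names no anticipated SD other than 2.61, and even on the kind reading the protection ends at about 2.62 after dropout, short of the upper end that the protocol cites.

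Second, 74% combines the highest cited SD with the full 10% dropout. The Data Analysis section plans to include all randomised participants and impute missing data, so 48 per arm is not the planned analysis set. This also stands. Imputation does not restore all the lost information, so the 48 and 54 columns serve as working bounds. At SD 2.7 they lie on either side of 80%; at 2.8 both are below it, the second only slightly. The detectable difference of 1.60 remains within the protocol's range of clinically important differences, 1.39 to 2.0.

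Third, a reader might take 74% as the power of the planned primary analysis. The documents do not support that. The primary analysis is a mixed model of change from baseline, and the article does not say whether the cited SDs are single-time-point or change SDs. Suppose 2.8 were a single-time-point SD, equal at both times. The SD of change would then be 2.8 × √(2(1 − r)), and power with 48 per arm would be about 66%, 74% or 83% for assumed pre-post correlations r of 0.4, 0.5 or 0.6. Power could move either way, so the model does not rescue the guarantee, and 74% should be presented only as the result of the same two-sample calculation. A condensed article may leave the correlation to the full protocol or analysis plan, so its absence is not a fault.

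**Conclusion.** The guarantee of adequate power under greater dispersion is not supported by the figures in the same section. After the planned dropout, 108 women give 80% power for 1.5 points up to an SD of about 2.61, with essentially no reserve. At SD 2.8 the same calculation gives about 74–75% with 48 evaluable per arm and about 79% with all 54. The shortfall is therefore about 5 to 6 points with full dropout and about 1 point without. These figures assume a two-sided 5% test, equal arms and a simple comparison of two means.

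A reader might go further and infer that the sample size is miscalculated, that the trial is underpowered, or that 2.61 was a poor choice. None of these follows. The 108 reproduces exactly, 2.61 is reasonably high within the cited range, and the documents do not show that the true SD exceeds it. The fault is one over-worded sentence, modest in size and worth correcting.

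**What to change.** Delete the sentence that guarantees power and replace it with a statement of this kind:

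*108 women give 80% power for a 1.5-point difference at SD 2.61 after 10% dropout; at SD 2.8, the top of the cited range, power in the same two-sample calculation is about 74% (about 79% without dropout).*

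The detectable difference at SD 2.8 with 48 per arm, about 1.6 points, can be added. The description of 2.61 as conservative may stay.

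The cost is a change of wording and a slightly less favourable power statement. Enrolment, analysis and conduct are unaffected. The article reports that data analysis has not started, so the statement can be corrected before any result is known. Nothing here requires the SD to be redefined for another analysis or a pre-post correlation to be stated.

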### Randomization, Allocation, and Blinding

The participants in the study will be randomly assigned to 1 of 2 groups: the IG (MI+AO+mobility exercises) or the CG (mobility exercises alone). All the participants will perform mobility exercises of the upper limb involving flexion, extension, abduction, adduction, internal rotation, and external rotation for approximately 20 minutes between 1 and 3 times a day 3 times a week for the duration of the intervention (6 weeks).

The randomization process will be carried out using the Research Randomizer tool and an allocation ratio of 1:1 with the aim of guaranteeing impartiality and validity in the study and ensuring a balanced distribution, simple randomization, and a reduction in biases while preserving the integrity and reliability of the results. The randomization list will be created by a member of the research team without contact with participants or access to personal or clinical information.

This is a single-blind study, as neither participants nor the researchers delivering the intervention can be blinded. Blinding will be maintained for the researchers responsible for collecting outcome data, administering evaluation instruments, and performing the statistical analyses.

### Intervention: the IM-OA23 Program

The study intervention is part of the IM-OA23 program, a structured initiative designed to integrate MI and AO into rehabilitation strategies. Support for the intervention will be presented in video format and will be accompanied by instructions for performing the MI and OA therapies as well as the additional mobility exercises, with a video prepared to help participants perform the therapies.

The intervention will last 6 weeks, during which the content of the program will be progressively modified. During the first 2 weeks, the following anatomical movements will be visualized and imagined, with an approximate duration of 20 seconds per movement: (1) arm flexion from 0 to 180°, (2) arm extension from 0 to −10°, (3) arm abduction from 0 to 180°, (4) arm adduction from 0 to 45°, (5) internal arm rotation from 0 to 45° with the elbow flexed at 90°, (6) external arm rotation from 0 to 45° with the elbow flexed at 90°, and (7) forward and backward arm circumductions (Figures1  2 [38]). In the third and fourth weeks, the participants will progress to performing the anatomical movements described above with a small weight, for example, a 1-kg dumbbell. The videos will depict a woman dressed in black in the frontal and lateral planes performing the described anatomical movements. In the final 2 weeks (fifth and sixth), the content will focus on ADLs through the following tasks: (1) reaching for a jar, (2) raising and lowering blinds, (3) drawing a curtain, (4) changing a light bulb, (5) stirring a pot, (6) scratching one’s back, (7) stretching, (8) putting on and taking off a coat, (9) hugging someone, (10) cleaning a window pane, (11) turning the steering wheel of a car, and (12) throwing a ball.

**Figure 1. F1:**
[figure not shown]
Anatomical movements performed [38].

**Figure 2. F2:**
[figure not shown]
Audiovisual resources developed. The images illustrate the exercises assigned for weeks 1 and 2.

For each of the movements and ADLs, AO will be performed first, followed by MI. After the completion of the MI and AO blocks, the participants will also carry out mobility exercises involving repeating the movements they saw in the videos.

As indicated, all the participants will perform upper-extremity mobility exercises involving flexion, extension, abduction, adduction, internal rotation, and external rotation. They will perform the mobility exercises for approximately 20 minutes per session between 1 and 3 times per day on 3 different days per week throughout the 6-week intervention period. The minimum dose will be 1 time per day on 3 different days per week, and the maximum dose will be 3 times per week on 3 different days per week.

Each participant will be instructed on how to access the audiovisual resources developed specifically for this study and hosted on a dedicated website (Figure 3). They will also receive an information sheet describing the exercises and a field diary to record the frequency of intervention practice during the established weeks. At the end of the explanation, the participant will be scheduled for data collection at 6 weeks (T1) and 3 months (T2).

